## Abstract

**Background:**

Significant lower genital tract (LGT) dysbiosis and an associated lower rate of clinical pregnancy after in vitro fertilization–frozen embryo transfer (IVF-FET) among polycystic ovary syndrome (PCOS) patients have been previously reported by our group. We aimed to assess whether transvaginal *Lactobacillus* supplementation can reverse LGT dysbiosis and further improve perinatal outcomes in PCOS patients after IVF-FET.

**Methods/design:**

This is a protocol for a multicenter, open-label, randomized controlled trial in China. Women diagnosed with PCOS who are undergoing IVF-FET treatment will be recruited. Allocation to the intervention/control arms at a ratio of 1:1 will be executed by an electronic randomization system. Participants in the intervention arm will receive the live *Lactobacillus* capsule vaginally for 10 consecutive days before embryo transfer, while those in the control arm will receive standard individualized care. The primary outcomes will be the clinical pregnancy rate, implantation rate, and live birth rate. 16S rRNA sequencing and liquid chromatography–mass spectrometry will be conducted to evaluate the LGT microbiome and systemic metabonomics before and after the intervention. A sample of 260 participants will provide 95% power to detect a 20% increase in the rate of clinical pregnancy (*α* = 0.025, one-tailed test, 15% dropout rate). A total of 300 participants will be recruited.

**Discussion:**

This is the first large and multicenter randomized controlled trial aimed at assessing the efficacy of transvaginal *Lactobacillus* supplementation on restoring the LGT microbiome and improving perinatal outcomes in PCOS patients after IVF-FET. This pragmatic trial is promising for increasing the rates of clinical pregnancy and live birth in PCOS patients after IVF-FET.

**Ethics and dissemination:**

Ethical review approval was obtained from the Medical Research Ethics Committees of the International Peace Maternity and Child Health Hospital of Shanghai Jiao Tong University (15 October 2020, GKLW 2020-29). To maximize dissemination, these findings will be reported in open access publications in journals with high impact, and oral and poster conference presentations will be performed.

**Trial registration:**

ChiCTR ChiCTR2000036460. Registered on 13 September 2020, https://www.chictr.org.cn/showproj.html?proj=59549.

**Supplementary Information:**

The online version contains supplementary material available at 10.1186/s13063-023-07825-9.

## Background

Polycystic ovarian syndrome (PCOS) is one of the most common endocrinopathies among women of reproductive age, affecting approximately 10–15% of women worldwide, and is one of the most common causes of female infertility [1, 2]. According to the Rotterdam criteria, two of the following three criteria must be fulfilled for a PCOS diagnosis: hyperandrogenism, oligo-ovulation or anovulation, and polycystic ovarian morphology defined by the presence of ≥ 12 follicles with a maximum diameter of 2–9 mm in either ovary [3, 4]. Women with PCOS are at a high risk of infertility due to anovulation. In vitro fertilization–frozen embryo transfer (IVF-FET) provides a valuable choice for PCOS patients who desire to become pregnant. However, once pregnant, women with PCOS are more susceptible to recurrent miscarriage, gestational diabetes mellitus (GDM), hypertension disorders in pregnancy, etc. [5, 6].

Our previous study showed that the bacterial genus diversity was higher in the lower genital tract (LGT), including the vagina and cervical canal, in PCOS patients. Additionally, the abundance of *Lactobacillus* spp. was significantly reduced in the LGT of PCOS patients. Pathway enrichment analysis showed that the top pathways were beneficial to the growth of pathogenic species, including *Gardnerella* [7]. Importantly, we found that in PCOS patients undergoing IVF-FET, those with *Lactobacillus* deficiency in the LGT had significantly lower rates of embryo implantation and clinical pregnancy (unpublished data), suggesting a potential role of reversing LGT dysbiosis in improving perinatal outcomes in PCOS patients after IVF-FET. However, large-scale and multicenter randomized clinical trials (RCTs) examining the effect of a vaginal *Lactobacillus* intervention on improving pregnancy outcomes in PCOS patients with LGT flora dysbiosis are unavailable.

The use of probiotics mainly containing *Lactobacillus* spp. was previously reported to have benefits in the treatment of vaginal diseases. A recent meta-analysis (*n* = 2321) showed that probiotic therapy resulted in a beneficial outcome in the treatment of bacterial vaginosis [8]. Compared with antibiotic therapy for bacterial vaginosis, which has high failure and recurrence rates, probiotics are recognized as valuable alternative strategies for their significant role in reestablishing the physiological vaginal environment and improving the local immune response with fewer adverse effects, further relieving clinical symptoms [9]. Moreover, a meta-analysis systematically reviewed the beneficial outcomes of probiotic treatment for women with GDM, including maternal and infant health and well-being [10].

PCOS patients were reported to have metabolic disorders, mainly hyperandrogenism, insulin resistance, dyslipidemia, and derangements in carbohydrate and hormonal metabolism [4, 11–15]. Moreover, studies reported that metabolic profiling and the vaginal microbiome were associated with adverse perinatal outcomes such as preterm birth [16]. However, the changes in metabonomics in the LGT and their interactions with systemic metabolic status in PCOS patients remain unknown, as do their effects on IVF–FET and maternal and infant health outcomes. Given the adverse perinatal effects of LGT dysbacteriosis on PCOS patients and the promising benefits of reversing LGT dysbacteriosis on improving the perinatal outcomes of PCOS patients, we designed this multicenter, open-label RCT to provide an accessible and effective therapy to better improve the perinatal outcomes and health of PCOS patients with LGT dysbiosis who are undergoing IVF–FET.

## Methods/design

### Objectives

We plan to conduct the present trial to evaluate the effects of supplementation with live *Lactobacillus* capsules for vaginal use on reversing LGT dysbiosis and improving perinatal outcomes in PCOS patients undergoing IVF-FET.

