### Proposed outcome measurement

#### Primary outcome

The clinical pregnancy rate will be the primary outcome. The clinical pregnancy rate is defined as the ratio of the clinical pregnancy (one or more observed gestational sacs with a fetal heartbeat in the uterus under ultrasonography 28 days after embryo transfer) to the number of transplant cycles.

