##### Neonatal outcomes

The birth defect rate is defined as the ratio of birth defects (fetal body structure, functional or metabolic congenital abnormalities) to the number of transplant cycles*.* Birth weight, infant sex, gestational age at birth, Apgar score, congenital anomalies, shoulder dystocia, bone fracture, neonatal hypoglycemia, bronchial plexus injury, neonatal respiratory distress, neonatal pathological jaundice, neonatal intensive care unit admission, stillbirth (≥ 20 weeks), and neonatal death (within the first 28 days after delivery) will be followed-up and assessed.

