### Statistical methods

#### Sample size calculation

A recent meta-analysis reported an estimated clinical pregnancy rate of 26% in PCOS patients undergoing IVF [24]. Our team has revealed that approximately 30% of PCOS patients have *Lactobacillus* deficiency (PCOS-LD), which presents as lower levels of *Lactobacillus* (< 50%) in the vagina [7]. Our unpublished data suggested a clinical pregnancy rate of 17.65% in patients with PCOS-LD, while a clinical pregnancy rate of 41.82% was reported in PCOS patients without *Lactobacillus* deficiency (PCOS-non-LD). Moreover, our team previously reported a clinical pregnancy rate of 49.69% in patients who underwent IVF due to tubal blockage [25]. To improve the clinical pregnancy rate among infertile PCOS-LD patients to the level of that among PCOS-non-LD patients, or even to the clinical pregnancy rate among patients with tubal blockage, we hypothesized a 20% increase in the clinical pregnancy rate in our RCT. Assuming a clinically important 20% increase in the rate of clinical pregnancy in the intervention arm and allowing for a 15% dropout rate, the calculated sample size of 260 subjects (130 per group) will provide 95% power with a one-tailed alpha error of 0.025. Thus, we aim to recruit 300 women in total (150 per group).

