#### Statistical analysis

Categorical variables will be presented as counts with percentages, e.g., *n* (%). Normally distributed data will be shown as the means with standard deviations, e.g., means ± SDs, while nonnormally distributed data will be expressed as medians with interquartile ranges, e.g., medians (IQRs). Student’s *t* test for continuous variables with normal distributions and the nonparametric

Kruskal–Wallis test for nonnormally distributed data will be applied for comparisons of significant differences between the 2 groups. The Pearson chi-square test will be used for categorical data. For binary observational endpoints, risk ratios with 95% confidence intervals will be calculated by binomial regression with and without adjustment for potentially confounding baseline values. In this study, the main analyses will be conducted using an intention-to-treat (ITT) model, in which all participants will be included based on random assignment regardless of study completion. For outcomes collected at different time points, a repeated measurements design using a generalized estimating equation (GEE) model will be used to fit outcomes that are measured at each time point so that all the participants might be included in the analyses, even if there are missing data for some of the follow-up points. A multiple imputation model will be used to process the missing data. Additionally, statistical analyses of the baseline characteristics of participants who remain in the study and those who are lost to follow-up will also be performed to explore whether there is differential dropout. All statistical analyses will be conducted using the SPSS software (version 25.0) and R software (version 4.0.2). A two-sided *p* value < 0.05 will be considered significant.

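### Complications and newborn measures that exist only after conception or birth, and have no stated denominator, go through plain two-group tests although the capsule is meant to change who conceives

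*Protocol article*

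**What the plan says.** The Objectives section of the protocol article seeks an effect of the capsule "for vaginal use on reversing LGT dysbiosis and improving perinatal outcomes in PCOS patients undergoing IVF-FET". The Background uses the word perinatal in two ways: for implantation and clinical pregnancy, and for outcomes such as preterm birth.

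The outcomes fall into two sets:

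- **Per transfer cycle.** "The clinical pregnancy rate will be the primary outcome", and it is defined per cycle. So are biochemical pregnancy, ongoing pregnancy, live birth, spontaneous abortion, preterm birth and birth defects.
- **No denominator.** Maternal outcomes includes gestational diabetes, hypertensive disorders, abruption, birth mode and blood loss. Neonatal outcomes includes "Birth weight, infant sex, gestational age at birth, Apgar score, congenital anomalies, shoulder dystocia, bone fracture, neonatal hypoglycemia", followed by items such as intensive care admission.

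Under Statistical analysis, the t test or Kruskal–Wallis test "will be applied for comparisons of significant differences between the 2 groups". Categorical data get a chi-square test, and binary endpoints get risk ratios. The main analyses are by intention to treat, missing data are multiply imputed, and two-sided p < 0.05 counts as significant. The section does not say how a woman without a pregnancy or a birth enters a comparison of, say, birth weight.

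**The concern.** A birth weight or an Apgar score is defined only where there is a birth, and gestational diabetes can be diagnosed only in a pregnancy. If the capsule raises conception, the women who reach those outcomes are a different selection in each arm. A comparison among them mixes any effect on the pregnancy with the effect on who became pregnant. Adjustment for baseline values does not restore randomisation, because unmeasured differences between the two groups of conceivers remain.

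The text leaves two ways to run the tests. Either women without a pregnancy or birth drop out, and the randomised comparison is lost. Or the imputation step, which does not separate missing from undefined values, generates birth weights for infants who never existed. In either case a significant difference could be reported as benefit or harm to mothers or infants when no pregnancy was changed, or a real effect could be hidden. The better the capsule works on the primary outcome, the less these comparisons can be trusted.

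**Working it through.** **Inputs from Sample size calculation.** Control rate: "Our unpublished data suggested a clinical pregnancy rate of 17.65% in patients with PCOS-LD". Alternative control rate: 26%, from a meta-analysis of PCOS patients undergoing IVF. Effect: "we hypothesized a 20% increase in the clinical pregnancy rate in our RCT". Size: "the calculated sample size of 260 subjects (130 per group) will provide 95% power with a one-tailed alpha error of 0.025", with 15% dropout and 300 recruited, 150 per group.

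**1. The plan's own figure, and which 20% is meant.** The two-proportion formula with pooled variance under the null is n = [1.960·√(2·p̄·(1−p̄)) + 1.645·√(p₁(1−p₁) + p₂(1−p₂))]² / (p₂−p₁)². With p₁ = 0.1765, p₂ = 0.3765 and p̄ = 0.2765:

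- n = (1.2397 + 1.0141)² / 0.04 = 127 per arm, total 254, against 260 stated.
- Power at 130 per arm is 95.4%.
- 254 / 0.85 = 299, against 300 recruited.

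The plan's figure therefore reproduces with an increase of 20 percentage points. A relative 20% increase would need 3,261 per arm.

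**2. Pregnancies expected.** With 150 per arm: 150 × 0.1765 = 26.5 and 150 × 0.3765 = 56.5, so about 26 and 56. About 300 − 83 = 217 women (72%) have no clinical pregnancy. At 26% to 46% the numbers are 39 and 69.

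**3. Share of additional pregnancies.** Assume no woman loses a pregnancy because of the capsule. The share f of intervention-arm pregnancies that occur only with the capsule is (p₂−p₁)/p₂:

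- 0.20 / 0.3765 = 53%
- 0.20 / 0.46 = 43%

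**4. Selection alone.** Suppose the capsule has no effect on complications, and additional pregnancies carry k times the risk of the others. The documents give no value for k, so the range is assumed. Among pregnant women the risk ratio is (1−f) + f·k. Per cycle it is that value times p₂/p₁.

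| k (assumed) | Among pregnant, 17.65%→37.65% | Among pregnant, 26%→46% | Per cycle, 17.65%→37.65% |
|---|---|---|---|
| 0.5 | 0.73 | 0.78 | 1.57 |
| 1 | 1.00 | 1.00 | 2.13 |
| 1.5 | 1.27 | 1.22 | 2.70 |
| 2 | 1.53 | 1.43 | 3.27 |

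For a continuous outcome, if babies from additional pregnancies were 100 g lighter (assumed) and both kinds of pregnancy reached birth equally often, the arms would differ by −100 × 0.53 = −53 g.

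**5. Per-cycle adverse outcomes.** The last column bears on preterm birth, spontaneous abortion and birth defects. With equal risk per pregnancy, the ratio is still 0.3765 / 0.1765 = 2.13. That is not selection; more women are pregnant and so can have the event.

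**The case against.** Much can be said for the plan, and part of it stands.

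- **A reader might infer that preterm birth will be compared among pregnancies and distorted by selection.** The documents do not support this. Preterm birth, spontaneous abortion and birth defects are defined per transfer cycle, which stays close to the randomised set apart from women with no transfer. Their difficulty is the one in step 5.
- **A reader might infer that no outcome counts a good result for every woman, so the perinatal objective cannot be answered.** That goes too far. Live birth and ongoing pregnancy per cycle come close to outcomes for all women, and the Background's looser use of perinatal covers conception. The same section also applies the word to preterm birth, and the Discussion ties it to risks once pregnant, so the health of the pregnancy is part of the objective.
- **The analysis set for secondary outcomes may be left to an analysis plan that is not shown.** This is fair for details. It does not settle the matter, because the article itself fixes the objective, outcomes, tests, threshold, intention-to-treat rule and imputation, and these do not fit together for a measure such as birth weight. Gestational diabetes could be counted per cycle, but it would then meet the problem in step 5.
- **The size of the bias rests on assumed risks.** This stands. The bias is zero if additional pregnancies carry the same risk, and its direction is unknown. The 17.65% rate also describes women below 50% Lactobacillus, whereas eligibility is below 80%, which is why the 26% scenario is shown too.
- **A term live birth outcome would not isolate perinatal health.** This also stands. With assumed preterm risks of 10% and 16% in the two kinds of pregnancy, and every conception counted as a birth, it would be 0.1765 × 0.90 = 15.9% against 0.1765 × 0.90 + 0.20 × 0.84 = 32.7%, with no pregnancy improved.

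**Conclusion.** The concern holds for outcomes that exist only after conception or birth and have no stated denominator: gestational diabetes, hypertensive disorders, birth mode, birth weight, gestational age, Apgar score and intensive care admission. As written, these are tested between groups at p < 0.05, with imputation that does not separate missing from undefined, although the trial hopes to raise conception by 20 points.

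Under the planning rates about half of intervention-arm pregnancies would be additional (53%, or 43% at 26% to 46%). Selection alone could then give risk ratios among pregnant women from 0.73 to 1.53. This rests on the assumed risk range of 0.5 to 2, on no woman losing a pregnancy because of the capsule, and on the hoped-for effect occurring. It shows what could happen and does not predict a bias of that size.

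Preterm birth, spontaneous abortion and birth defects per cycle are outside this point, except that a ratio near 2.13 would arise from more pregnancies alone and should not be read as harm. The primary outcome is unaffected. The change should be made because it is cheap and prevents a non-randomised efficacy claim.

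**What to change.** 1. In Statistical analysis, state that comparisons restricted to pregnant women or born infants are non-randomised and descriptive. Report them as estimates with 95% confidence intervals, and do not use them to claim that the capsule improves perinatal outcomes.
2. State that values undefined for lack of a pregnancy or birth are not imputed.
3. Rest the randomised perinatal claim on an outcome defined for every randomised woman from data already collected: live birth, supplemented by live birth at 37 weeks or later, with no pregnancy counted as no. Note that it mostly reflects conception.
4. Show adverse rates per cycle and per pregnancy side by side, so that an excess due only to more pregnancies is not read as harm.
5. Align the Objectives wording with this.

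The cost is wording and one derived variable, with no new visit, sample or participant. The downside is that differences in birth weight, Apgar score, intensive care admission and gestational diabetes can no longer be presented as treatment effects.

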### Study design and setting

This proposed study is a prospective, multicenter, open-label RCT. A total of 300 eligible participants will be recruited from 4 different tertiary hospitals, including ± 100 participants from the International Peace Maternity and Child Health Hospital, ± 50 participants from Ruijin Hospital, ± 50 participants from Zhongshan Hospital, and ± 100 participants from ShangHai JIAI Genetics and IVF Institute. A flowchart of participant enrollment and screening, randomization, and follow-up and sample collection is shown in Fig. 1.

**Fig. 1 Fig1:**
[figure not shown]
Flowchart for recruitment, screening, allocation, intervention, and follow-up of study participants. PCOS, polycystic ovary syndrome; qPCR, quantitative polymerase chain reaction; FET, frozen embryo transfer; HCG, human chorionic gonadotropin

### Participants

#### Inclusion criteria

A total of 20- to 35-year-old women who have been diagnosed with PCOS according to the Rotterdam Criteria and plan to undergo IVF–FET will be recruited. Quick screening of the abundance of *Lactobacillus* spp. will be performed by real-time quantitative polymerase chain reaction (RT–qPCR), which will be specified later. Women with PCOS with *Lactobacillus* spp. accounting for less than 80% of the vaginal microbiome who volunteer to participate will be eligible for this study.

#### Exclusion criteria

We will exclude individuals if they have been diagnosed with the following disorders: Cushing’s syndrome, congenital adrenal hyperplasia, thyroid disorder, hyperprolactinemia, androgen-secreting tumors, congenital malformations of the reproductive tract, systemic lupus erythematosus or any other autoimmune disease, HIV, endometriosis, uterine fibroids or colpitis. The subjects should not receive hormones, antibiotics, or vaginal medication within 7 days or cervical treatment or flushing within 5 days of the start of the study. Moreover, sexual activities should not be carried out within 48 hours. Women who undergo preimplantation genetic testing will also be excluded.

### Withdrawal of participants

Participants will be clearly informed by investigators at enrollment that they may withdraw from this RCT at any period for any reason without penalty. A withdrawal statement will be provided and signed. Written consent forms will be obtained if the individual agrees to receive continued follow-up for associated clinical outcomes after withdrawal.

### Procedure

The study procedure is described by following the Standard Protocol Items: Recommendations for Interventional Trials (SPIRIT) checklist (Additional file 1).

### Recruitment and randomization

The clinical research coordinators (CRCs) will verbally inform PCOS patients that the hospital is currently conducting a multicenter clinical trial to better improve the outcomes of IVF–FET in PCOS patients with vaginal microbiota dysbiosis. If they fully understand and are willing to take part in the study, they will meet a CRC in person at the hospital, sign an informed consent form, and officially join the study on the first day of the current IVF–FET cycle. The CRCs will later inform patients of whether they have vaginal microbiota dysbiosis. Basic information, including sociodemographic characteristics and clinical history, will be collected by the CRCs using standardized questionnaires and recorded into an online and password-protected electronic data collection system (Clinical Research Integrated Platform [CRIP], https://crip-ec.shdc.org.cn, supported by Shanghai Hospital Development Center, Shanghai, China), which will automatically generate a sequential code and randomly allocate participants to the intervention group or the control group at a ratio of 1:1 based on the whole study population. The research doctors will manage the study group allocation. Given the nature of vaginal use of live *Lactobacillus* capsules before FET, the investigators and participants will be informed of the assignment. To ensure the reality of this study, independent statisticians will be recruited, and they will be blinded to the group allocation.

